# The ACHRU-CPP versus usual care for older adults with type-2 diabetes and multiple chronic conditions and their family caregivers: study protocol for a randomized controlled trial

**DOI:** 10.1186/s13063-017-1795-9

**Published:** 2017-02-06

**Keywords:** Type-2 diabetes mellitus, Randomized controlled trial, Pragmatic, Hybrid effectiveness-implementation design, Self-management, Group-based programs, Community-based settings, Health-related quality of life, Older adults

## Abstract

**Background:**

Many community-based self-management programs have been developed for older adults with type-2 diabetes mellitus (T2DM), bolstered by evidence from randomized controlled trials (RCTs) that T2DM can be prevented and managed through lifestyle modifications. However, the evidence for their effectiveness is contradictory and weakened by reliance on single-group designs and/or small samples. Additionally, older adults with multiple chronic conditions (MCC) are often excluded because of recruiting and retention challenges. This paper presents a protocol for a two-armed, multisite, pragmatic, mixed-methods RCT examining the effectiveness and implementation of the Aging, Community and Health Research Unit-Community Partnership Program (ACHRU-CPP), a new 6-month interprofessional, nurse-led program to promote self-management in older adults (aged 65 years or older) with T2DM and MCC and support their caregivers (including family and friends).

**Methods/design:**

The study will enroll 160 participants in two Canadian provinces, Ontario and Alberta. Participants will be randomly assigned to the control (usual care) or program study arm. The program will be delivered by registered nurses (RNs) and registered dietitians (RDs) from participating diabetes education centers (Ontario) or primary care networks (Alberta) and program coordinators from partnering community-based organizations. The 6-month program includes three in-home visits, monthly group sessions, monthly team meetings for providers, and nurse-led care coordination. The primary outcome is the change in physical functioning as measured by the Physical Component Summary (PCS-12) score from the short form-12v2 health survey (SF-12). Secondary client outcomes include changes in mental functioning, depressive symptoms, anxiety, and self-efficacy. Caregiver outcomes include health-related quality of life and depressive symptoms. The study includes a comparison of health care service costs for the intervention and control groups, and a subgroup analysis to determine which clients benefit the most from the program. Descriptive and qualitative data will be collected to examine implementation of the program and effects on interprofessional/team collaboration.

**Discussion:**

This study will provide evidence of the effectiveness of a community-based self-management program for a complex target population. By studying both implementation and effectiveness, we hope to improve the uptake of the program within the existing community-based structures, and reduce the research-to-practice gap.

**Trial registration:**

ClinicalTrials.gov, Identifier: NCT02158741. Registered on 3 June 2014.

**Electronic supplementary material:**

The online version of this article (doi:10.1186/s13063-017-1795-9) contains supplementary material, which is available to authorized users.

## Background

The prevalence of diabetes is increasing in countries across the globe, particularly type-2 diabetes mellitus (T2DM) [1]. Currently, 347 million people have diabetes worldwide and this is expected to increase by 55% by 2035 [1, 2]. T2DM comprises 90% of all diabetes cases [3] and results from genetic, behavioral, and environmental risk factors [1, 4]. Advancing age is associated with T2DM, with older adults having the highest prevalence of T2DM of any age group [1, 5]. Among older adults, T2DM frequently occurs in conjunction with other comorbidities [1, 6, 7]. Studies suggest that upwards of 40% or more people with T2DM have three or more comorbid health conditions [8–10]. When considered within the context of other comorbidities, T2DM represents a significant burden in older adults that is linked to higher mortality, reduced functional status, increased use of health care services, and higher risk of institutionalization [5, 11]. Thus, there is an urgent requirement to provide services that meet the needs of this complex population.

There is strong evidence that the primary determinants of T2DM, notably smoking, poor diet, obesity, and physical inactivity are modifiable through self-management activities [2, 12–17]. From large clinical trials, such as the American Diabetes Prevention Program (DPP) [18] and the Finnish Diabetes Prevention Study (FDPS) [19, 20], there is evidence that lifestyle and weight-loss programs can reduce the incidence of diabetes by up to 58%. The benefits can be enduring [4]; one study reported a 34% reduction in incidence rates among its intervention group during a 10-year follow-up [21] and a 4-year study reported sustained weight loss and improved cardiovascular risk factors following intensive lifestyle intervention [22]. Thus, aggressive public policy initiatives have been recommended to encourage self-management of lifestyle change [23]. Strong support for these initiatives can be found in a recent systematic review showing that integrated care interventions for people with T2DM (which target self-management and patient-centered, team-based approaches to care) can result in improvements in a range of clinical and patient-reported outcomes, with no studies reporting a worsening in outcomes [24].

Clinic-based lifestyle interventions like the DPP and FDPS require substantial resources (e.g., specialized expertise, individual settings); thus, researchers have assessed whether interventions delivered in community settings might be an effective, economical, and feasible alternative. Recent international studies, for example, have reported that group-based diabetes programs, established in community settings, result in improved clinical, lifestyle, and psychosocial outcomes compared to routine care [25–27]. Importantly, community-based programs have proven to be scalable and sustainable at a national level [28] and they are beneficial to individuals of many ages, including older adults [29–31]. In a systematic review involving 16 studies that translated the DPP into hospital, primary care, community, and work settings Whittemore [32] concluded that programs linked to existing structures of care, (e.g., the Young Men’s Christian Association, or YMCA) may enhance adoption, implementation, and maintenance of the program.

While there is strong evidence for self-management interventions in general, the existing research, particularly for community-based interventions, has limitations. Notably, evidence for their effectiveness is equivocal. Whittemore [32] concluded that self-management interventions delivered in community settings, despite their ability to reach diverse populations, reported less weight loss than those interventions offered in more restricted settings, such as hospitals. In contrast, studies by Ali et al. [33] and Ruggiero et al. [34] found that interventions with community components (e.g., lay members or community health workers) resulted in more weight loss compared to those run by medical or allied health professionals. A different challenge relates to validity and reliability since many effectiveness studies of community-based interventions rely on single-group designs and/or pilot studies with small samples [35]. Additionally, comparatively few studies have examined the effectiveness of lifestyle interventions in older adults with T2DM and comorbid conditions, because this population is typically excluded from randomized controlled trials (RCTs) [5, 36]. With their increased risk of comorbidity and geriatric syndromes, such as cognitive impairment, falls, and depression [37–40], this medically complex population is typically more difficult to reach, recruit, and retain [7]. Thus, there is uncertainty about the clinical effectiveness of self-management interventions for older adults with multiple chronic conditions (MCC). More information is also needed on adapting community-based interventions to individual settings, the effectiveness of interventions in key patient subgroups, and operational costs.

The purpose of this article is to describe a study designed to examine the effectiveness and implementation of the Aging, Community and Health Research Unit-Community Partnership Program (ACHRU-CPP), a new 6-month interprofessional, nurse-led program to promote self-management in older adults (aged 65 years and older) with T2DM and MCC and their family caregivers (including family and friends). The description follows the Standard Protocol Items: Recommendations for Interventional Trials (SPIRIT) guidelines [41], which provide a list of the recommended items to include in clinical trial protocols. The populated SPIRIT Checklist is available in Additional file 1. The trial is a multisite, two-arm, pragmatic, mixed-methods RCT that employs a type-2 hybrid design which simultaneously evaluates both clinical effectiveness (e.g., Does the intervention work?) and implementation (e.g., Is the intervention delivery feasible and acceptable?) [41]. The participant timeline recommended by SPIRIT [41] shows the schedule of enrollment, interventions, and assessments (see Fig. 1) and these are all discussed in greater detail below. Hybrid designs are thought to facilitate the transition from research to practice and result in more rapid uptake of effective interventions [42]. The trial is based on a pilot study, where the program’s feasibility and potential effectiveness were demonstrated [43].

**Fig. 1 Fig1:**
[figure not shown]
Standard Protocol Items: Recommendations for Interventional Trials (SPIRIT) Checklist: schedule of enrollment, interventions, and assessments

### Objectives

The aim of the trial is to evaluate the clinical effectiveness and implementation of the ACHRU-CPP, compared to usual care. We hypothesize that clients in the intervention group will experience greater improvements in health-related quality of life (HRQoL) compared to the usual care group. We also expect that the program will improve outcomes for family caregivers, improve interprofessional team functioning among the interventionists, and be feasible to implement in practice at no additional cost. The study will address the following specific objectives:To compare the effects of the intervention versus usual care on older adults’ HRQoL, diabetes self-management, self-efficacy, depressive symptoms, anxiety, and the costs of use of health services (from a societal perspective)To determine the subgroups of older adults that benefit most from the programTo compare the effects of the intervention versus usual care on family caregivers’ HRQoL, strain, depressive symptoms, and the costs of use of health services (from a societal perspective), andTo evaluate the implementation of the program and its effects on interprofessional/team collaboration

## Methods/design

This study is a pragmatic RCT which combines a quantitative analysis of the effects of the intervention with a qualitative and quantitative analysis of the implementation and contextual factors potentially associated with variations in the outcomes in the real world. Combining quantitative and qualitative analyses in an intervention study has been referred to as a concurrent, embedded mixed-methods design in the mixed-methods literature [44] and a hybrid trial in the interventions literature [42]. The choice to include both quantitative and qualitative methods in our study reflects our view that no single method can fully answer the questions posed by an intervention study. While an RCT is regarded as the “gold standard” for establishing effectiveness of interventions, effect sizes do not provide policy-makers with information on how an intervention might be replicated in their specific context, or whether trial outcomes can be reproduced. Guidelines for evaluating complex interventions have been updated to recognize the value of using qualitative research methods to complement the quantitative effects [45].

Figure 2 provides the overall evaluation framework for the trial. The evaluation of effectiveness and implementation outcomes, while discussed separately below, will occur simultaneously, receive equal emphasis, and are recognized as often dependent on each other (e.g., the effectiveness of the intervention will depend on the quality and success of the implementation strategy and process). Our approach of assigning equal weight to the effectiveness and implementation components of the study is consistent with a type-2 hybrid trial [42]. Implementation outcomes examined in the trial are guided by two published frameworks: the broad implementation research framework by Peters et al. [46] and the Consolidated Framework for Implementation Research (CFIR) for systematically identifying contextual factors that can impact intervention implementation, adoption and maintenance by Damschroder et al. [47]. The Peters et al. [46] framework recognizes a range of implementation outcomes including: acceptability, adoption, appropriateness, feasibility, fidelity, cost, coverage, and sustainability. The CFIR provides a focused set of constructs to evaluate barriers and facilitators including characteristics of the intervention, outer and inner setting, individuals delivering the intervention, and the implementation process. We have developed research questions and quantitative measures and/or qualitative inquiries corresponding to each implementation outcome from these two frameworks.

**Fig. 2 Fig2:**
[figure not shown]
Type-2 hybrid effectiveness – Implementation evaluation framework

### Participants and setting

A strategic first step for this study was the development of a partnership between researchers in the Aging, Community and Health Research Unit (ACHRU) at McMaster University (Hamilton, ON, Canada) and the University of Alberta (Edmonton, AB, Canada), program coordinators from seven community-based organizations, and seven diabetes education centers (Ontario) or primary care networks (Alberta). The study will enroll 160 participants in each of two Canadian provinces, Ontario and Alberta. Although these provinces are in the same country, they encompass diverse characteristics in terms of geography (Ontario is in the east, Alberta the west), culture, and health care system structure. In Ontario, study participants will be recruited from clients who have been recently referred for diabetes-related services to diabetes education centers (DECs). DECs are regional centers that provide ongoing diabetes education programs, counselling and follow-up sessions by registered nurses (RNs) and registered dietitians (RDs) for clients and their families. In Alberta, study participants will be recruited from clients who have been recently referred to diabetes or chronic disease management programs at three primary care networks (PCNs). PCNs are centralized resource facilities that provide equipment and health care teams to service clients from physician clinics in close proximity to one another. The Ontario and Alberta provinces were selected to compare and contrast different health care systems. The specific sites within each province were selected because they serve a large and growing older adult population, and demonstrated strong support for the program. Community partner organizations were selected and invited based on existing collaborations with the sites and/or interest in health promotion for community-dwelling older adults. The community partners were also selected based on availability and accessibility of an appropriate space to host monthly group program sessions and availability of staff members to participate in program delivery (e.g., a program coordinator for the group sessions).

In order to participate in the study, clients must satisfy the following inclusion criteria:have enrolled in a DEC (Ontario) or referred to a PCN (Alberta) within the past 24 months, or recruited from the community65 years of age or olderdiagnosed with at least two chronic conditions in addition to T2DMnot planning to move away from the community in the next 6 months, andable to speak English (or with an interpreter available)

These inclusion criteria were designed to be minimally stringent in order to facilitate the broad applicability of the results to the general population of community-dwelling older adults with T2DM and MCC. Aspects of specific criteria were also selected to ensure consistency with broader research initiatives.

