### Sample size

The sample size for the RCT was calculated to detect a minimally important difference (MID) in the primary outcome measure (PCS-12). The developers suggest that the MID for interpretation of group mean PCS-12 score differences is approximately 3.0, which corresponds to an effect size of 0.30 [56]. However, the developers also acknowledge that this MID estimate is a matter of ongoing debate. Robust research on effect sizes seen across a range of studies using a variety of quality-of-life measures has shown that the mean effect size is remarkably consistent at 0.50, or half the standard deviation [57]. This effect size is close to the one observed in our pilot study, which was 0.40 [43].

We based our estimate of the sample size on an effect size of 0.50, 5% alpha, 80% power and 20% attrition (18% was observed in our pilot study). Using these assumptions, the sample size was 80 (each) for the intervention and control groups.

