### Randomization design

After providing written, informed consent and completing the baseline questionnaires, participants will be randomly assigned to either the intervention or the control arm of the study using a 1:1 allocation ratio. Stratified permuted block randomization will be used to assign participants to the control and intervention groups. Study sites are expected to be relatively homogeneous regarding client sociodemographic and clinical characteristics and the delivery of intervention and usual care services. However, to minimize the confounding effects of possible differences among the study sites, the sites will be used as a stratum. The randomized sequence at each site will be based on assignments of blocks randomly selected from sizes of 2, 4, or 6. A biostatistician not involved in the recruitment process will generate the random number assignments for each site using SAS Version 9.3. Random number sequences will be input into a centralized web-based randomization service (REDCap) that will allocate clients to the control or intervention group at each site in accordance with the sequence.

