### Analyses

#### Analysis of participants

The data collected will be screened for accuracy, missing data, outliers, and statistical assumptions. SAS Version 9.3 will be used for all statistical analyses. All statistical tests will be performed using two-sided tests at the 0.05 significance level. For all models, the results will be expressed as effects, standard errors, 95% confidence intervals, and associated *p* values. The evaluation will be conducted in accordance with the intention-to-treat principle; therefore, imputation (using multiple imputation) will be used to address missing data and compare these results with the complete case analysis. If there are discrepancies between the multiple imputation and complete case results, we will conduct a sensitivity analysis using different multiple imputation methods (appropriate for the pattern of missingness) to see how robust the analysis is for the chosen method(s) of handling missing data [85]. This procedure will result in multiple data sets and models being run on each data set. Appropriate methods will be used to combine the results to generate pooled parameter estimates, standard errors, and confidence limits.

An analysis of baseline (*T*1) data will be performed to compare the demographic and clinical characteristics of the intervention and control groups. This analysis will confirm whether the two groups are equal on these variables. Means and standard deviations will be generated for continuous variables, and frequencies and proportions for categorical variables. The appropriate significance test (e.g., *t* test for continuous measures, chi-square for categorical) will be applied to identify any significant differences between the groups. Significant differences will be adjusted for in the outcomes analyses.

For the analyses relating to clients, *t* tests will be used to compare the changes in primary and secondary outcomes from baseline (*T*
_1_) and 6 months (*T*

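### The enrolment total is given as 160 in the Abstract and as 160 per province (320) in the Methods, and the sample-size section does not say which its 80 per arm refers to

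*Protocol article*

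**What the plan says.** Three places in the protocol article bear on the size of the trial.

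- Abstract, Methods/design: "The study will enroll 160 participants in two Canadian provinces, Ontario and Alberta". Read plainly, this is 160 in all.
- Participants and setting: "The study will enroll 160 participants in each of two Canadian provinces, Ontario and Alberta". Read plainly, this is 320 in all.
- Sample size: the calculation is introduced as one for the trial ("The sample size for the RCT was calculated to detect a minimally important difference (MID) in the primary outcome measure (PCS-12"), its inputs are listed ("We based our estimate of the sample size on an effect size of 0.50, 5% alpha, 80% power and 20% attrition"), and the result is that "the sample size was 80 (each) for the intervention and control groups". Two arms of 80 make 160. The section says neither that this is the whole trial nor that it applies to each province.

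Other sections describe one trial. Randomization design has a single scheme, stratified by site, "using a 1:1 allocation ratio". Analysis of participants compares the two groups by t test, includes site as a predictor in the ANCOVA, and adds a comparison between Ontario and Alberta. No section mentions 320, doubles the calculation, or describes two separately powered provincial trials.

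**The concern.** The two enrolment sentences differ only in the words that turn a total into a per-province figure, and the totals they imply differ by a factor of two. Both stand in complete running prose, so neither text extraction nor an amendment history explains the difference.

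The total fixes when recruitment ends across the sites and what difference the primary comparison of change in PCS-12 can detect. It also sets how much information there is for the comparison of the two provinces, whose differing health systems are given as a reason for choosing them. A reader of the article cannot tell which size of trial is being run.

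**Working it through.** **Inputs.** From Sample size: standardised difference d = 0.50, alpha 5%, power 80%, attrition 20%. From Analysis of participants: "All statistical tests will be performed using two-sided tests at the 0.05 significance level". From Randomization design: equal allocation. From the Abstract and Participants and setting: a total of 160 or 320.

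**Step 1: reproduce the stated sample size.** With the normal approximation, n per arm = 2(z₀.₉₇₅ + z₀.₈₀)²/d² = 2(1.960 + 0.842)²/0.25 = 62.8, rounded up to 63. The two-sample t test gives 63.77, rounded up to 64. Allowing for attrition, 64/(1 − 0.20) = 80 per arm, or 160 for one two-arm comparison. The plan's figure reproduces exactly.

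**Step 2: the total under each sentence.**

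| Source | Reading | Total | Per arm | Completers per arm (× 0.8) |
|---|---|---|---|---|
| Abstract | 160 across both provinces | 160 | 80 | 64 |
| Participants and setting | 160 in each province | 2 × 160 = 320 | 160 | 128 |

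Sample size gives 80 per arm. That agrees with the Abstract if it is the whole trial, and with Participants and setting if it is per province.

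**Step 3: what one pooled comparison can detect.** Approximately, power = Φ(d√(m/2) − 1.96), where m is completers per arm.

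- m = 64: 0.50 × √32 = 2.83, and Φ(0.87) = 0.807. The t test gives 0.801. The difference detectable with 80% power is 0.50 SD.
- m = 128: 0.50 × √64 = 4.00, and Φ(2.04) = 0.979. The t test also gives 0.979. The difference detectable with 80% power is 0.35 SD.

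**Step 4: one province taken alone.** If 160 in total were split equally between the provinces, each would have 40 per arm enrolled and 32 completers per arm. Then 0.50 × √16 = 2.00, and Φ(0.04) = 0.516; the t test gives 0.504, so about 50% power at 0.50 SD. The equal split is an assumption that the document does not state. It mentions seven centres or networks, of which three are Alberta primary care networks. If 160 were enrolled in each province, a province alone would have the 80% of the m = 64 case.

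**The case against.** The strongest reply is that this is probably one slip of wording and that nothing statistical is broken. Much of that stands. The sample-size arithmetic is right, and under neither total does the pooled primary comparison fall below 80% power at 0.50 SD.

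Three stronger readings are tempting, and the document does not support them.

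- A reader might infer that the stated power is contradictory. It is not. It appears once, as 80%, and matches 80 per arm. What is open is whether it belongs to the trial or to each province.
- A reader might infer that the primary analysis population is defined in two conflicting ways, or that the primary test is to be run twice at 0.05. Intention to treat is stated once, and no section describes two primary tests. The single randomization scheme and site as a predictor fit one trial. Whether the comparison is pooled needs saying only if 320 is the intended total.
- A reader might take Sample size to settle the matter at 160 in total. It does not use the word total, and on a per-province reading it agrees with Participants and setting.

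Two further limits are fair. The protocol never claims that a comparison within one province is powered, so the 50% figure illustrates what that total means and is not a failed standard. Power at effects smaller than 0.50 SD is a question about the choice of effect size, separate from this one.

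The reply does not remove the conflict. The Abstract and Participants and setting give different totals, and no other text says which is meant. An article may leave much to a fuller document, but here it states the figure itself, in two incompatible ways.

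**Conclusion.** The enrolment total is contradictory as written: 160 in the Abstract and 320 in Participants and setting. The 80 per arm in Sample size is arithmetically correct for one comparison at 0.50 SD, but its scope is not stated. The contradiction is confined to the enrolment total and does not extend to the stated power or the analysis population.

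Its size is a factor of two in enrolment. For a pooled primary comparison, that is 80% against about 98% power at 0.50 SD, or a difference detectable with 80% power of 0.50 SD against about 0.35 SD. These figures assume equal allocation, attrition of exactly 20% in each arm, and a two-sided two-sample t test at 0.05. The single-province figure also assumes an equal provincial split. The document alone cannot show which total is intended.

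**What to change.** State one total and use it consistently.

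- **If the total is 160:** change only Participants and setting, so that it gives 160 as the sum across Ontario and Alberta. The Abstract and Sample size already fit.
- **If it is 160 per province:** correct the Abstract to 320 in total, 160 per province. In Sample size, state either that 80 per arm was calculated for each province, or that the pooled trial has 160 per arm (128 completers, about 98% power at 0.50 SD and 80% at about 0.35 SD). State also whether the primary comparison is pooled or made by province.

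The cost is one phrase in the first case, and a correction to the Abstract plus a sentence or two in Sample size in the second. Neither adds participants beyond the total already intended.
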